## Methods

### Trial design

This is a single-center, randomized, double-blind, blank-controlled trial with 3 groups: the control group, the “PDT once” group, and the “PDT twice” group. The curative effect will be compared statistically across groups. There will be 126 participants in total, with 42 in each group. The trial will be conducted at the Rheumatology and Immunology Department at the Integrated Hospital of Traditional Chinese Medicine, Southern Medical University. Further details can be seen in the flowchart of the trial design in Fig. 1.

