### Groups and sample size

The necessary sample size was estimated to be 99 based on a preliminary trial with a small sample size. During the preliminary phase, eighteen participants were included and randomly divided into 3 groups of 6. According to the protocol, differences in UCSS between week 8 and the baseline value were detected. The mean ± standard deviation of UCSS reduction was obtained at week 8 and week 0 individually: 0.33±0.817, −0.80±0.837, −1.0±1.000. The standard deviation was 0.873, and PASS 11 software was used to estimate the sample size by means of the following formula:

$$ 1-\beta =1- probF\;\left[{F}_{1-a,G-1,N-G,}\;\left(G-1\right),N-G, NV/{\sigma}^2\right] $$

The significance level, *α*, was set to 0.05; the power of a test, 1 − *β*, was 0.80; the number of groups, *G*, was 3; *N* represents the sample size; *V* represents the variance of the group averages, $$ V=\Sigma \left({\left({\mu}_i-\overline{\mu}\right)}^2\right)/G $$; σ represents the standard deviation.

A total of 126 participants will be included to allow for 20% loss to follow-up. There will be 3 groups:
Control group: (*n*=42) These individuals will receive micro-arthroscopic surgical procedures twice (day 0 and 4th week), and 0.9% saline will be administered instead of PS.PDT once group: (*n*= 42) Participants will receive PDT on day 0, followed by 0.9% saline administration instead of PS in the 4th week.PDT twice group: (*n*=42) Individuals will receive PDT twice: once on day 0 and once in the 4th week.

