### Outcome and safety measures

#### Outcome measures

Primary outcome measure

The Ultrasound Compound Score of Synovitis (UCSS) will be calculated according to the EULAR-OMERACT combined scoring system for grading synovitis in rheumatoid arthritis [11]. Improvement in the UCSS compared with the control group will be the primary endpoint.
(2)Secondary outcome measures
Clinical evaluation of knee joints: The circumference will be measured 2 cm above the upper edge of the patella, and joint flexion and extension will be measured to assess the range of motion.DAS28-ESR: DAS28-ESR= 0.56 × the total number of tender joints + 0.28 × the total number of swollen joints + 0.70 × ln(ESR) + 0.014 × general health assessment score.Antibody levels: Serum will be collected by centrifugation, and then the RF and anti-CCP antibodies will be detected by a standard commercially available test kit.Inflammation indicators: Serum will be obtained by centrifugation, and then ESR and CRP will be detected by standard commercially available test kits.X-ray: X-rays of the knee joint will be used to evaluate bone destruction.Pathological biopsies of synovial tissue: The synovium of the joint, which will be acquired before laser irradiation during each operation, will be fixed, embedded by dehydration, and sectioned. The synovium will be stained with hematoxylin and eosin for histological evaluation, and synovial histopathology will be observed, including synovial cell proliferation, inflammatory cell infiltration, and angiogenesis (pannus formation). The pathological biopsy of synovial tissue will strictly follow the clinical diagnostic protocol. The research nurses will collect specimens with special specimen boxes, record basic information on the subjects, and then send specimens to the pathology department for testing and preservation as soon as possible.

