#### Statistical analysis

SPSS 20.0 statistical software will be used to analyze the measurement data, described as the means ± standard deviations ($$ \overline{x}\pm s $$), and the main evaluation index (improvement in the UCSS compared with the baseline value) will be analyzed by single-factor variance analysis among the three groups. ANOVA will be used for repeated measurement data of the secondary evaluation indicators to explore the principal and interactive effects of grouping and time. Multiple paired *t*-tests comparing two time points (before and after treatment) will be used to analyze repeated measurements. Single-factor ANOVA will be used to compare the differences at the same time points after treatment between the three groups. Differences will be statistically significant at *P* <0.05.

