### Strengths and limitations of this study

The aim of this trial is to evaluate the short-, medium-, and long-term clinical efficacy of PDT in the treatment of RRA synovial hyperplasia and synovitis with a 1-year follow-up.An improvement in the UCSS value compared with the baseline will be the primary endpoint based on the EULAR-OMERACT combined scoring system for grading synovitis in RRA.PDT has the advantages of minimal trauma, stronger targeting, fewer side effects, and definite curative effects, which makes it more acceptable to patients than steroid injections or arthroscopic synovectomy.The trial will take place at only a single center.

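### The primary endpoint is a comparison with control, but the only primary test and the sample size use a three-group omnibus F, with no PDT-versus-control contrast or testing rule named

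*Protocol article*

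**What the plan says.** All references are to the protocol article.

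- **Outcome measures:** "Improvement in the UCSS compared with the control group will be the primary endpoint".
- **Strengths and limitations of this study:** "An improvement in the UCSS value compared with the baseline will be the primary endpoint".
- **Trial design:** "The curative effect will be compared statistically across groups". There are three arms (control, PDT once, PDT twice), and no contrast is named.
- **Statistical analysis:** the main index, UCSS change from baseline, "will be analyzed by single-factor variance analysis among the three groups". For comparisons at individual visits: "Single-factor ANOVA will be used to compare the differences at the same time points after treatment between the three groups". The only decision rule is one sentence, beginning "Differences will be statistically significant at", which sets P below 0.05.
- **Groups and sample size:** the size comes from a noncentral F formula for three groups. Alpha "was set to 0.05" and power "was 0.80; the number of groups" set at 3. The result is 99 evaluable and 126 enrolled.

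The two endpoint statements can be read together: change from baseline is the variable, and comparison with control is the question asked of it. The only multiple tests mentioned are before-and-after paired t-tests within patients, which do not compare PDT with control.

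**The concern.** With two active arms, improvement relative to control is two questions: does PDT once beat control, and does PDT twice beat control? The omnibus F answers neither. It has no direction, gives control no special role, and can be significant because of any pattern among the three means. The trial could therefore meet its only stated primary criterion without having tested either regimen against control.

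This matters because the Discussion wants to learn about treatment frequency and arrive at a standard therapy, which needs a conclusion about a particular regimen. It also leaves open, after the data are seen, which comparison becomes the headline result. And the 80% power quoted for the trial is not power for the comparison the endpoint names.

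**Working it through.** **Inputs (Groups and sample size).** Pilot week-8 changes in UCSS are 0.33, −0.80 and −1.0, taken in the order control, once, twice. SD 0.873, alpha 0.05, power 0.80, G = 3. Evaluable N is 99 (33 per arm) and loss is 20%.

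**1. The plan's own figure.** Power = 1 − probF[F(0.95; 2, N−3); 2, N−3, λ], with λ = N·V/σ² and V = Σ(μᵢ − μ̄)²/3.

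| Control mean | μ̄ | V | Smallest N with equal arms | λ at N = 99 | F power at N = 99 |
|---|---|---|---|---|---|
| +0.33 (printed) | −0.49 | 0.3429 | 27 | 44.5 | >99.9% |
| −0.33 (assumed) | −0.71 | 0.0789 | 99 | 10.2 | 81.2% |

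The printed means do not give 99; a control mean of −0.33 gives it exactly. The sign is an inference and a separate matter to reconcile, so both readings are carried forward. Enrolment is consistent with 99: 33/0.8 = 41.25, rounded up to 42 per arm, and 3 × 42 = 126.

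**2. Power for the contrasts the endpoint names, 33 per arm.** Standard error = 0.873 × √(2/33) = 0.215. Noncentrality is the difference divided by 0.215.

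| Reading | Contrast | Difference | Noncentrality | Unadjusted 0.05 | Dunnett |
|---|---|---|---|---|---|
| Control −0.33 | once vs control | 0.47 | 2.19 | 58% | 48% |
| Control −0.33 | twice vs control | 0.67 | 3.12 | 87% | 81% |
| Control +0.33 | once vs control | 1.13 | 5.26 | 99.9% | >99.8% |
| Control +0.33 | twice vs control | 1.33 | 6.19 | >99.9% | >99.9% |

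The critical value on 96 df is 1.98 unadjusted and about 2.24 with Dunnett. On the printed means, a Bonferroni level of 0.025 still gives 99.8% and >99.9%.

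**3. How often F and the contrasts disagree** (simulation, 33 per arm, pooled variance).
- Control mean −0.33: F is significant while once versus control is not (at 0.05) in about 25% of trials. F is significant with neither control contrast significant in less than 0.1%.
- Illustrative means, assumed here, of 0 for control and +0.3 SD and −0.3 SD for the PDT arms: F is significant with neither control contrast significant in 17%.

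**4. Family-wise error with no true effect** (simulation, 33 per arm).

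| Procedure | Chance of any false positive |
|---|---|
| Omnibus F alone | 5.0% |
| Three pairwise tests, only after significant F | 5.0% |
| Two control contrasts, only after significant F | 4.1% |
| Two control contrasts, regardless of F | 9.0% |
| Three pairwise tests, regardless of F | 12.1% |

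If once equals control and only twice differs, the gated test of once versus control has an error of 4.6% to 5.0%. The gate works because with exactly three groups F followed by pairwise tests (Fisher's protected LSD) is a closed procedure.

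**The case against.** A reader might infer that the plan runs pairwise tests with uncontrolled error, more than doubling the false-positive rate. The article does not support that. It states no between-group pairwise tests, and if they followed a significant F the error would be held at 5%. Even ungated, the two control contrasts give 9.0%, which is 1.8 times 5%; only ungated testing of all three pairs (12.1%) exceeds double. It is also true that the article states no gate, so its flat P rule neither requires protected testing nor excludes ungated testing. Undefined is the accurate word.

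A reader might also infer that the trial is underpowered for PDT once. That depends entirely on the sign of the pilot control mean. On the printed value there is no shortfall. On −0.33 most of it is not caused by multiplicity: power is already 58% with no adjustment and falls to 48% with Dunnett.

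Other points for the plan: on its own effects, F almost never reaches significance without at least one control contrast doing so; a post-hoc method could sit in an unseen analysis plan; and the Background calls this a pilot. These lower the severity. They do not remove the mismatch, because the article is not silent: it names the primary test and sizes the trial on it, and neither matches the endpoint in Outcome measures. A later plan could add contrasts, but the stated power would still be power for F.

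**Conclusion.** The mismatch between endpoint and test holds on the text alone and needs no assumption about effect sizes: a significant F would not establish that either PDT regimen is better than control, and no contrast or testing rule is stated that would.

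The sizes are conditional. The 9% and 12% error rates apply only if pairwise tests are run whatever F shows. The 58% and 87% powers (48% and 81% with Dunnett), and the 25% of trials with a significant F but an unproven once-versus-control effect, assume a control mean of −0.33, SD 0.873, the stated arm order and 33 per arm. On the printed +0.33 both contrasts have at least 99.8% power even at 0.025.

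This should be fixed before analysis. It is not a fatal flaw, since the data to be collected already support the right analysis.

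**What to change.** Make the primary analysis two prespecified contrasts from the same ANOVA model, PDT twice versus control and PDT once versus control, in place of the omnibus F. Control the error by either:

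- Dunnett's procedure for the two contrasts; or
- a fixed sequence: twice versus control at 0.05 and, only if that is significant, once versus control at 0.05.

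Report once versus twice as an estimate with a 95% CI and no significance claim; that still informs the treatment-frequency question. Restate the power for these contrasts once the sign of the pilot control mean has been reconciled.

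**Cost.** Wording only, with no new data. Under Dunnett the critical value rises from 1.98 to about 2.24. Under the fixed sequence, once versus control goes untested if twice versus control fails. On the −0.33 reading, twice versus control in the fixed sequence has 87% power, above the 81% for F, while once versus control cannot exceed 58%. Reaching 80% for once versus control at 0.05 would then need 56 per arm (168 evaluable; 56/0.8 = 70, so 210 enrolled). On the printed means no increase is needed.

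### Before-after paired t-tests are listed as P<0.05 tests beside the between-group analyses; they ignore the randomised control and should be descriptive only

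*Protocol article*

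**What the plan says.** The Statistical analysis section of the protocol article names four analyses:

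- The main index, change in the ultrasound synovitis score (UCSS) from baseline, is compared among the three arms by one-way ANOVA.
- "ANOVA will be used for repeated measurement data of the secondary evaluation indicators", to examine group and time main effects and their interaction.
- Multiple paired t-tests "comparing two time points (before and after treatment) will be used to analyze repeated measurements".
- One-way ANOVA compares the three arms at each post-treatment time point.

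The section closes with a single P<0.05 criterion that covers all of these. It does not call the paired tests descriptive, does not say which arms or outcomes they cover, and gives no rule for what prevails if they disagree with the between-group tests.

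On numbers, Groups and sample size states "The necessary sample size was estimated to be 99" and "A total of 126 participants will be included to allow for 20% loss to follow-up". Table 2 schedules four post-baseline assessments, at weeks 4, 8, 24 and 48.

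**The concern.** A paired t-test asks whether the mean in one set of patients moved from its own baseline. It does not ask whether PDT moved it more than the sham procedure did. Several features of this trial could move all three arms together without any PDT effect:

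- Entry requires current knee swelling and a minimum ultrasound and/or MRI synovitis score (Table 1), so some regression to the mean is to be expected.
- All patients receive background anti-rheumatic treatment (Intervention).
- Controls have the arthroscopic procedure twice, with saline in place of the photosensitiser (Groups and sample size), and the procedure includes joint lavage (Intervention).

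The sham arm is there to subtract these influences, and a before-after P-value leaves them in. The pattern most easily misread is a significant change in a PDT arm and a non-significant change in control. That contrast is not a test of the difference between arms, and it arises often by chance when the arms are truly alike. The Background says that clinical effectiveness of PDT in RA has not yet been reported, so such a pattern could carry undue weight.

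**Working it through.** **1. The plan's own figures.** The inputs from Groups and sample size are alpha 0.05, power 0.80, three groups, SD 0.873 ("The standard deviation was 0.873") and pilot changes of "0.33±0.817, −0.80±0.837, −1.0±1.000". The power formula uses noncentrality N·V/σ², where V is the variance of the group means.

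- As printed, the mean of means is (0.33 − 0.80 − 1.0)/3 = −0.49. V = (0.82² + 0.31² + 0.51²)/3 = 1.0286/3 = 0.343. The formula then gives N = 27 (power 0.84), not 99.
- With the first mean taken as −0.33, the mean of means is −0.71. V = (0.38² + 0.09² + 0.29²)/3 = 0.2366/3 = 0.0789. The formula gives N = 99, or 33 per arm (power 0.81).
- Loss to follow-up: 33/0.8 = 41.25, rounded up to 42 per arm and 126 in total. This reproduces.

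The sign discrepancy is a separate matter. Here these figures supply only the SD (0.873) and the two arm sizes: 33 (planned evaluable) and 42 (enrolled).

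**2. Set-up of the illustration.** The true mean change is assumed identical in all three arms, so there is no PDT effect. The SD of change is 0.873. This is a UCSS value used as a stand-in, because the article gives no SD for any secondary outcome. Tests are two-sided at 5%. The common change is assumed to be 0.3 points, with a range of 0.2 to 0.5.

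**3. One arm's paired test.** The noncentrality is (change/SD)·√n.

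- n = 33: (0.3/0.873)·√33 = 1.97, significant in 48% of trials.
- n = 42: (0.3/0.873)·√42 = 2.23, significant in 59% of trials.

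These rates come from 20,000 simulated trials per setting.

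**4. Misleading pattern.** Let p be the per-arm rate. The arms are independent, so the probability that control is not significant and at least one of the two PDT arms is significant equals (1 − p)·[1 − (1 − p)²].

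- n = 33, p = 0.483: 0.517 × (1 − 0.517²) = 0.38.
- n = 42, p = 0.587: 0.413 × (1 − 0.413²) = 0.34.

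**5. Range over the assumed common change.**

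| Common change | Per-arm paired test, n=33 / n=42 | PDT arm significant, control not, n=33 / n=42 | Between-group ANOVA of change, n=33 / n=42 |
|---|---|---|---|
| 0 | 5% / 5% | 9% / 9% | 5% / 5% |
| 0.2 | 25% / 30% | 33% / 36% | 5% / 5% |
| 0.3 | 48% / 59% | 38% / 34% | 5% / 5% |
| 0.4 | 72% / 82% | 25% / 17% | 5% / 5% |
| 0.5 | 89% / 95% | 11% / 5% | 5% / 5% |

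The row for 0 uses p = 0.05: 0.95 × (1 − 0.95²) = 0.09. The misleading pattern peaks for small to moderate shared changes. With larger changes every arm, control included, tends to be significant. The between-group test is unaffected throughout.

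**The case against.** The strongest reply is that the same section plans analyses that do use the randomised control: group and group-by-time effects, and a between-group ANOVA at each visit. The primary index is also compared among arms. A reader might infer that secondary efficacy rests on the before-after tests, or that shared improvement will be credited to PDT. The document does not say so. It gives the paired tests no stated priority and does not say how their results will be read. This part of the objection stands and limits the severity. It does not remove the point, because the paired tests share the P<0.05 criterion and nothing makes them subordinate.

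A reader might also infer a complete-case analysis that discards a fifth of the patients. That is not supported either:

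- No missing-data method or analysis population is stated, and an article may leave both to the full protocol or SAP.
- The 20% is a sample-size allowance. If it were fully used, 126 × 0.8 = 100.8 patients would remain, against 99 planned.
- The visit-by-visit ANOVAs can use everyone measured at that visit.
- Nothing in the article says that those who leave would be poor responders.

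What remains is conditional. If classical repeated-measures ANOVA is run with listwise deletion, a patient who misses one visit is dropped from that analysis altogether.

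Finally, the size depends on assumed inputs. As printed, the first pilot group moved in the opposite direction to the other two, which does not support improvement in every arm. The value that reproduces N = 99 has the other sign, but the article does not settle this. The 0.3-point change is therefore an illustration and not an estimate. The total number of paired tests is not given, so no overall false-positive count can be fixed.

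**Conclusion.** The point holds in a limited form. The article prescribes before-after paired t-tests at P<0.05 without marking them descriptive, and such tests cannot isolate a PDT effect in this design. Under an assumed shared 0.3-point improvement with SD 0.873 and no PDT effect, each paired test is significant in about 48% (33 per arm) to 59% (42 per arm) of trials. A PDT arm is significant while control is not in about 34% to 38%, whereas the between-group ANOVA stays near 5%. These figures rest on the assumed change, on a UCSS SD standing in for the secondary outcomes, and on the paired tests being run arm by arm.

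Severity is modest. Valid between-group comparisons are already planned, and the weakness mainly affects secondary inference.

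**What to change.** - Report within-arm change descriptively, as mean change with a confidence interval, and use no within-arm P-value as evidence of efficacy.
- Add one sentence stating that efficacy conclusions rest only on between-group comparisons.
- Preferably, replace classical repeated-measures ANOVA with one mixed model for repeated measures, with arm, visit, arm-by-visit and baseline value as terms. Report PDT-minus-control differences at weeks 8, 24 and 48 with confidence intervals. The model keeps the observed visits of patients who miss others, which matters because the plan itself allows for 20% loss. SPSS can fit it.

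The first two changes are wording only. The third costs slightly more analysis work and brings a missing-at-random assumption that should be stated. No extra data are needed.

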### Evaluation procedure

The researchers will record participants’ postoperative improvement and general condition, including body temperature and respiration, pulse, and heart rate, during face-to-face follow-up visits. The items evaluated during each follow-up visit are shown in Table 2. All the data will be uploaded to the case report form (CRF) by rigorously trained data collectors. To reduce the rate of loss to follow-up, we will also communicate with participants by a variety of methods, including WeChat, telephone, text message, and e-mail, to remind them to return for further examination.

**Table 2 Tab2:** Follow-up plan

***Follow-up time***	***Evaluation index***
*Baseline*	*UCSS, clinical evaluation of knee joints, DAS28, antibody levels, inflammation indicators, X-ray, routine blood test, routine urine test, blood biochemical test, infectious disease screening*
*W0* *(first operation)*	*Pathological biopsies of synovial tissue*
*W4±3 d* *(second operation)*	*UCSS, clinical evaluation of knee joints, DAS28, antibody levels, inflammation indicators, pathological biopsies of synovial tissue*
*W8±3 d*	*UCSS, clinical evaluation of knee joints, DAS28, antibody levels, inflammation indicators, blood biochemical test*
*W24±5 d*	*UCSS, clinical evaluation of knee joints, DAS28, antibody levels, inflammation indicators*
*W48±5 d*	*UCSS, clinical evaluation of knee joints, DAS28, antibody levels, inflammation indicators, X-ray*

*W* week, *d* days

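### The between-group ANOVA at each follow-up visit names no baseline term, so secondary knee measures and DAS28 lose precision that their collected baseline values could supply

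*Protocol article*

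**What the plan says.** The Statistical analysis section of the protocol article sets out four analyses:

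- **Primary index.** "the main evaluation index (improvement in the UCSS compared with the baseline value) will be analyzed by single-factor variance analysis among the three groups". The reference to baseline is explicit.
- **Secondary indicators over time.** "ANOVA will be used for repeated measurement data of the secondary evaluation indicators to explore the principal and interactive effects of grouping and time".
- **Before versus after.** Multiple "paired *t*-tests comparing two time points (before and after treatment) will be used to analyze repeated measurements". These compare no groups.
- **Groups at a visit.** "Single-factor ANOVA will be used to compare the differences at the same time points after treatment between the three groups". This sentence names no outcome, baseline covariate or change score.

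Under Outcome measures, the knee assessment is defined by absolute measurements: "The circumference will be measured 2 cm above the upper edge of the patella, and joint flexion and extension will be measured". DAS28-ESR is likewise defined as a score at a visit. The baseline row of Table 2 (Evaluation procedure) begins "UCSS, clinical evaluation of knee joints, DAS28, antibody levels, inflammation indicators, X-ray, routine blood test", and the knee evaluation and DAS28 recur at weeks 4, 8, 24 and 48. Every patient therefore has a scheduled baseline value for each of these outcomes.

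**The concern.** A one-factor model has group as its only term. Applied to knee circumference after treatment, it sets different people's limbs against each other, and much of the spread in circumference is body build rather than synovitis. Patients also differ in range of motion and DAS28 before treatment. The information that would remove this stable variation is collected but not used in this test.

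The wording is a stated choice of method. The same paragraph refers the primary index to baseline and does not do so here.

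At stake is the precision of the secondary comparisons at individual visits. Circumference and range of motion are the clinical measurements of the knee itself, and a modest fall in swelling could be missed at a given visit. In any one trial, a chance baseline imbalance would also pass into the visit estimates. Its standard error between two arms of 42 is √(2/42) = 0.22 between-person SD.

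**Working it through.** **Inputs from the article.** Three groups, 1:1:1; 42 randomized per group, and 99/3 = 33 per group from the stated requirement; "The significance level, *α*, was set to 0.05"; the noncentral-F power formula under Groups and sample size, with noncentrality λ = N·V/σ².

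**Inputs not in the article.** No SD, effect size or baseline correlation is given for circumference, range of motion or DAS28. The article therefore has no figure for this test to reproduce. Its planning statement, "the power of a test, 1 − *β*, was 0.80", concerns UCSS. The values of r and the effect below are assumptions.

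**Step 1: variances.** With between-person variance σ² at each time and correlation r between baseline and visit, the variance per patient is:

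- post-treatment value: σ²
- change from baseline: 2(1−r)σ²
- baseline-adjusted (ANCOVA): (1−r²)σ²

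So post-treatment/ANCOVA = 1/(1−r²), and change/ANCOVA = 2(1−r)/(1−r²) = 2/(1+r).

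| r | post-treatment/ANCOVA | change/ANCOVA |
|---|---|---|
| 0.5 | 1.33 | 1.33 |
| 0.7 | 1.96 | 1.18 |
| 0.8 | 2.8 | 1.11 |
| 0.9 | 5.3 | 1.05 |
| 0.95 | 10.3 | 1.03 |

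Below r = 0.5 a change score is less precise than the post-treatment value. ANCOVA is at least as precise as either at every r, apart from one degree of freedom.

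**Step 2: power for one assumed effect.** Both PDT arms shift by 0.3 between-person SD, so the means are (0, −0.3, −0.3), the overall mean is −0.2, and V = (0.04 + 0.01 + 0.01)/3 = 0.02. With 33 per arm, post-treatment values give λ = 99 × 0.02/1 = 1.98. ANCOVA at r = 0.9 gives λ = 1.98/0.19 = 10.4.

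| | 33 per arm | 42 per arm |
|---|---|---|
| post-treatment values | 22% | 27% |
| ANCOVA, r = 0.7 | 39% | 49% |
| ANCOVA, r = 0.8 | 53% | 64% |
| ANCOVA, r = 0.9 | 82% | 91% |

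At 33 per arm, the post-treatment test keeps 22/39 = 56% of the adjusted power at r = 0.7 and 22/53 = 42% at r = 0.8.

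**Step 3: the same check anchored at 80%.** Choose the effect so that ANCOVA has 80% power with 33 per arm. The post-treatment test then has 76% at r = 0.3, 67% at 0.5, 60% at 0.6, 50% at 0.7, 37% at 0.8, 21% at 0.9 and 13% at 0.95. It falls below half of 80% somewhere between r = 0.7 and r = 0.8.

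**Step 4: by outcome (two arms of 42, assumed values).**

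- Circumference, SD 4 cm, difference 1 cm, r = 0.90 to 0.95: post-treatment 21%, ANCOVA 75% to 96%.
- DAS28, SD 1.0 to 1.3, difference 0.6, r = 0.3 to 0.7: post-treatment 56% to 79%, ANCOVA 60% to 97%. At r = 0.3 the loss is only 3 to 4 points (79% against 82%; 56% against 60%). At r = 0.7 it is 18 to 28 points (79% against 97%; 56% against 84%).

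**The case against.** **The plan already has a between-group test that can use baseline.** If baseline is one of the time levels, which the article does not say but which is natural, stable limb size drops out of the group-by-time term. Take the Step 2 effect as constant after treatment, with five time points, equal correlations and 33 per arm. The interaction test then has 31% power at r = 0.7, 46% at 0.8 and 82% at 0.9, against 39%, 53% and 82% for ANCOVA at one visit. This stands: a reader might infer that a real fall in swelling would go undetected by the plan as a whole, and the article does not support that. However, the interaction is a global test. It does not say at which visit, or for which PDT arm, a difference from control lies.

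**The word *differences* may mean change scores.** That reading is possible. The separate assignment of before-after comparison to paired tests, and the explicit baseline reference for the primary index alone, make post-treatment values likelier without settling it. On the change reading the loss is small once r is high.

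**The short-, medium- and long-term aims do not rest on this test.** A reader might infer that they do, since it compares groups visit by visit. The Abstract ties those time frames to UCSS improvement at weeks 8, 24 and 48, relative to baseline. The point concerns secondary outcomes only.

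**A post-treatment comparison is valid.** Under randomization it is unbiased, and its type I error rate already allows for chance imbalance. That stands; this is a loss of precision. Covariates are often left to an analysis plan, but here the article itself names a one-factor method.

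**Conclusion.** The point holds as a matter of efficiency. As written, the visit-wise ANOVA does not use baseline values that every patient is scheduled to provide. On the likelier reading, the variance penalty is 1.33 to 5.3 over r = 0.5 to 0.9; on the change-score reading it is 1.33 to 1.05 over the same range.

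It is tempting to say that all these secondary results lose most of their power. The article does not support that. A loss of more than half needs r of about 0.8 or higher. This is plausible for knee circumference, but it is not shown for range of motion or DAS28, and the limb-size argument does not apply to DAS28 at all. All sizes rest on assumed correlations and effects. The direction does not: baseline adjustment is at least as precise under either reading, apart from one degree of freedom.

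**What to change.** Replace the visit-wise sentence for these outcomes with wording such as:

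> At weeks 4, 8, 24 and 48, knee circumference, flexion, extension and DAS28 will be compared between groups by analysis of covariance, with the same patient's baseline value as covariate (for knee measures, the baseline value of the same knee). Adjusted differences, each PDT group minus control, will be reported with 95% confidence intervals.

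This also settles whether values or changes are analyzed. Moving to plain change scores would not be an equivalent repair, because they are less precise than post-treatment values when r is below 0.5. The repeated-measures ANOVA can stay as the global test, with a statement of whether baseline is one of its time levels.

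The cost is one sentence of analysis wording and one covariate in the planned software, with no new patients, visits or measurements. The downside is one degree of freedom and the assumption of a linear relation to baseline. The change should be made before unblinding.
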